| Scientific title                              | 0.01% atropine eyedrops in children with myopia and intermittent exotropia (AMIXT): a randomized clinical trial                                                 |
| Countries of recruitment                      | China                                                                                                                                                           |
| Health condition(s) or problem(s) studied     | myopia, intermittent exotropia                                                                                                                                  |
| Intervention(s)                               | Active comparator: 0.01% atropine sulfate                                                                                                                       |

|                                      |                                                                                                                                                                                                                                                                                                                                                                                                                                                                                                                                                                                                                                                                                                                                                                                                                                                                                                                                                                                                                                                                                                                                                                                                                                                                                                                                                                                                                                                                                                                                                                                                                                                                                                                                                                                                                                                                                                                                                                                                                                                                                                              |
|--------------------------------------|--------------------------------------------------------------------------------------------------------------------------------------------------------------------------------------------------------------------------------------------------------------------------------------------------------------------------------------------------------------------------------------------------------------------------------------------------------------------------------------------------------------------------------------------------------------------------------------------------------------------------------------------------------------------------------------------------------------------------------------------------------------------------------------------------------------------------------------------------------------------------------------------------------------------------------------------------------------------------------------------------------------------------------------------------------------------------------------------------------------------------------------------------------------------------------------------------------------------------------------------------------------------------------------------------------------------------------------------------------------------------------------------------------------------------------------------------------------------------------------------------------------------------------------------------------------------------------------------------------------------------------------------------------------------------------------------------------------------------------------------------------------------------------------------------------------------------------------------------------------------------------------------------------------------------------------------------------------------------------------------------------------------------------------------------------------------------------------------------------------|
|                                      | Placebo comparator: 1% hydroxypropyl methylcellulose                                                                                                                                                                                                                                                                                                                                                                                                                                                                                                                                                                                                                                                                                                                                                                                                                                                                                                                                                                                                                                                                                                                                                                                                                                                                                                                                                                                                                                                                                                                                                                                                                                                                                                                                                                                                                                                                                                                                                                                                                                                         |
| Key inclusion and exclusion criteria | 
Inclusion criteria
 
 
1) age 6-12 years old;
 
2) basic-type IXT meeting all the following criteria: 
 
(a.) intermittent or constant exotropia at distance (6 m), and either an IXT or exophoria at near (33 cm);
 
(b.) exodeviation magnitude of <math>\geq 10</math> prism diopters (PD) at distance measured by the prism and alternate cover test (PACT);
 
(c.) near/distance deviation difference of <math>\leq 10</math> PD;
 
 
 
3) myopia <math>\leq -0.5</math> diopters (D) and <math>> -6</math> D in both eyes based on cycloplegic spherical equivalent (SE);
 
4) distant best-corrected visual acuity (BCVA) of <math>\leq 0.2</math> logarithms of the minimum angle of resolution (logMAR) in each eye as measured using Early Treatment for Diabetic Retinopathy Study (ETDRS) charts.
 
 
Exclusion criteria
 
 
1) having known contraindications or sensitivity to atropine;
 
2) with serious health problems or cognitive disability affecting follow-up or ability to cooperate with examinations;
 
3) having astigmatism with cycloplegic cylinder <math>\geq 2</math> D in either eye;
 
4) participating in other interventional trials;
 
5) having undergone any myopia control lenses including orthokeratology, rigid gas-permeable contact lenses, progressive addition spectacle lenses, or other lenses, except for single-vision eyeglasses;
 
6) with previous use of atropine within 6 months;
 
7) having active ocular inflammation in either eye;
 
8) with peripheral anterior chamber depth <math>< 1/3</math> corneal thickness;
 
9) having intraocular pressure (IOP) <math>> 21</math> mmHg in either eye;
 
10) diagnosed of ocular diseases or having clinically significant abnormal findings in the ocular examinations;
 
11) unwilling to follow up for 2 years.
 
 |
| Study type                           | 
Interventional
 
Allocation: 2:1 randomized
                                                                                                                                                                                                                                                                                                                                                                                                                                                                                                                                                                                                                                                                                                                                                                                                                                                                                                                                                                                                                                                                                                                                                                                                                                                                                                                                                                                                                                                                                                                                                                                                                                                                                                                                                                                                                                                                                                                                                                                                                                                      |

|                        |                                                                                                                                                                                                                                                                                                                                                                                                                                                                                                                                                                                                                                                                           |
|------------------------|---------------------------------------------------------------------------------------------------------------------------------------------------------------------------------------------------------------------------------------------------------------------------------------------------------------------------------------------------------------------------------------------------------------------------------------------------------------------------------------------------------------------------------------------------------------------------------------------------------------------------------------------------------------------------|
|                        | Intervention model: parallel assignment
Masking: double-blind (subject, investigator)
Primary purpose: treatment                                                                                                                                                                                                                                                                                                                                                                                                                                                                                                                                                    |
| Target sample size     | 300                                                                                                                                                                                                                                                                                                                                                                                                                                                                                                                                                                                                                                                                       |
| Primary outcome(s)     | Change in cycloplegic SE from baseline at 1 year.                                                                                                                                                                                                                                                                                                                                                                                                                                                                                                                                                                                                                         |
| Key secondary outcomes | 1) Cycloplegic SE change from baseline at 2 years.
2) Change from baseline in axial length, monocular function (BCVA, near vision, accommodative amplitude [AA] and photopic/mesopic pupil size), exotropia conditions (distant/near magnitude of exodeviation and distant/near exotropia control), binocular vision (distant/near stereoacuity, near point of convergence [NPC], accommodative convergence/accommodation [AC/A] ratio, and fusional vergence amplitude [FVA]) and safety parameters (intraocular pressure [IOP] and corneal endothelial cell density [ECD]) at 1 year and 2 years.
3) Change in choroidal parameters and higher-order aberrations. |

50

### 51 **3. Introduction**

52 Intermittent exotropia (IXT) is one of the most common types of strabismus,  
53 particularly in Asian countries, which is characterized by an intermittent  
54 outward deviation of one or both eyes. The prevalence of IXT was reported to  
55 be 1.0% in the United States and up to be 3.2% in Asia.

56 Exotropia and myopia are commonly coexistent. The myopia prevalence  
57 rate in exotropia population was reported to reach 57.7%, much higher than  
58 that in children without strabismus (12.3%) in 12-year-old Australian children.  
59 A cross-sectional study of 9970 children aged 6 to 72 months in the  
60 Multi-Ethnic Pediatric Eye Disease Study (MEPEDS) in southern California  
61 and the Baltimore Pediatric Eye Disease Study (BPEDS) in Maryland revealed

a higher prevalence rate of myopia in exotropia (12.7%) than that in children without exotropia (4.6%). The coexistence of myopia and IXT is commonly observed, but their relationship remains controversial. On one hand, myopia has been identified as a risk factor for concomitant exotropia. It is thought that myopia is associated with a decreased demand for accommodation, and hence lower convergence and a predisposition for developing exotropia. Subsequent population-based studies support this viewpoint, with myopia found to increase the risk of IXT development by 5.2 times. On the other hand, IXT has been regarded as a risk factor for myopia onset and progression. It was reported that more than 90% of IXT patients would develop myopia by 20 years old, which was much higher than that in non-strabismus population. In patients with IXT, additional accommodative convergence is required to maintain binocular vision and ocular alignment due to insufficient fusional convergence, which might give rise to increased accommodative loads and hence myopia progression. Alternately, it was proposed that increased convergence demand (via convergence accommodation/convergence) rather than accommodation contributes to myopia development in IXT. Whatever the exact mechanism is, myopia and IXT are closely related. Due to divisive definitions of exotropia deterioration, the natural history of IXT remains controversial. In the past decade, several prospective and multicenter clinical studies, especially the Pediatric Eye Disease Investigator Group (PEDIG), recommended observation as a preferable option for patients of IXT with good

exotropia control, stable magnitude of exodeviation, and mild psychological pressure. Thus, increased attention and further investigation are warranted in the management of myopia progression in children with IXT.

Atropine is an emerging pharmacological method for controlling myopia progression. The Atropine for the Treatment of Myopia (ATOM) study proposed 0.01% atropine as a comparably effective and less visually disruptive concentration than 0.1% and 0.5% atropine for myopia control. Since then, 0.01% atropine has been increasingly used in clinical practice for myopia control in Asia in recent years. The Low-Concentration Atropine for Myopia Progression (LAMP) study compared the efficacy of various low concentrations of atropine in slowing myopia progression and axial elongation, with 0.05% identified as the optimal concentration. While the safety and efficacy of low-concentration atropine have been repeatedly validated in non-strabismus population, there lacks evidence regarding that in population with myopia and IXT. As all the relative clinical trials before excluded participants with strabismus, whether the accommodative changes induced by atropine would impose any influence on exotropia conditions or binocular vision remains unknown. For safety, we will start with a relatively low concentration (0.01%).

## **4. Objectives**

### **4.1 Primary objective**

To evaluate the efficacy of 0.01% atropine eyedrops in slowing myopia progression in children with myopia and IXT.

## **4.2 Secondary objective**

### **4.2.1 Key secondary objective**

To determine the effect of 0.01% atropine eyedrops on exotropia conditions in children with myopia and IXT.

### **4.2.2 Other secondary objective**

To determine the effect of 0.01% atropine eyedrops on monocular function, binocular vision, and safety parameters in children with myopia and IXT.

## **4.3 Exploratory objective**

To explore the mechanism of 0.01% atropine eyedrops in controlling myopia progression.

# **5. Materials and methods**

## **5.1 Study design**

The study will be a 2-year, single-center, randomized, double-masked, and placebo-controlled trial, with a 2:1 allocation to intervention (0.01% atropine eyedrop) or placebo (1% hydroxypropyl methylcellulose).

## **5.2 Setting**

The enrollment and follow-up of all trial participants will be at the Department of Ophthalmology, the First Affiliated Hospital with Nanjing Medical University, Nanjing, Jiangsu, China.

### 5.3 Scheme

Figure 1. Study flow diagram.

[figure not shown]

### 5.4 Participants adherence

Compliance of administration of atropine or placebo eyedrops is evaluated based on the eyedrop diary, number of empty mono-dose containers returned, and inquiries on times of missed administrations at each visit. Individuals who used 75% or more of the prescribed medication is considered to have good compliance.

### 5.5 Eligibility

#### Inclusion criteria

- 1) age 6-12 years old;
- 2) basic-type IXT meeting all the following criteria:

- (a.) intermittent or constant exotropia at distance (6 m), and either an IXT or exophoria at near (33 cm);
  - (b.) exodeviation magnitude of  $\geq 10$  prism diopters (PD) at distance measured by the prism and alternate cover test (PACT);
  - (c.) near/distance deviation difference of  $\leq 10$  PD;
- 3) myopia  $\leq -0.5$  diopters (D) and  $> -6$  D in both eyes based on cycloplegic spherical equivalent (SE);
  - 4) distant best-corrected visual acuity (BCVA) of  $\leq 0.2$  logarithms of the minimum angle of resolution (logMAR) in each eye as measured using Early Treatment for Diabetic Retinopathy Study (ETDRS) charts.

**Exclusion criteria**

- 1) having known contraindications or sensitivity to atropine;
- 2) with serious health problems or cognitive disability affecting follow-up or ability to cooperate with examinations;
- 3) having astigmatism with cycloplegic cylinder  $\geq 2$  D in either eye;
- 4) participating in other interventional trials;
- 5) having undergone any myopia control lenses including orthokeratology, rigid gas-permeable contact lenses, progressive addition spectacle lenses, or other lenses, except for single-vision eyeglasses;
- 6) with previous use of atropine within 6 months;
- 7) having active ocular inflammation in either eye;
- 8) with peripheral anterior chamber depth  $< 1/3$  corneal thickness;

- 9) having intraocular pressure (IOP) >21 mmHg in either eye;
- 10) diagnosed of ocular diseases or having clinically significant abnormal findings in the ocular examinations;
- 11) unwilling to follow up for 2 years.

## **5.6 Sample size**

The sample size is determined using PASS 15 (NCSS, Utah) assuming: (1) the annual reduction of SE as 0.59 D in the 0.01% atropine group and 0.81 D in the control group according to results of the LAMP study; (2) the common standard deviation (SD) is assumed as 0.57 D in each group; (3) randomization to 0.01% atropine group and placebo control group is 2:1. The trial needs 160 participants in the 0.01% atropine group and 80 participants in the control group to provide 80% power (at 5% type I error rate) for detecting a clinically relevant difference of 0.22 D in SE progression at 12 months. To account for an expected drop-out rate of 20% over the 12 months follow-up period, the total number of participants for enrollment is 300 participants (200 in 0.01% atropine group and 100 in placebo control group).

## **5.7 Randomization and masking**

Eligible participants will be 2:1 randomized to receive 0.01% atropine or placebo eyedrops by use of a block randomization scheme with a fixed block size of six. Randomization will be completed by one unmasked investigator using sealed envelopes that contain randomized numbers. The random allocation sequence is generated using randomized block methods in the

Statistical Package for the Social Sciences (R Foundation for Statistical Computing. <https://www.R-project.org/>) by a statistician who is not involved in participant recruitment or data collection. Other investigators, participants, and the statistician will be masked to study allocation.

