## **5.8 Study intervention and termination**

All eyedrops (0.01% atropine sulfate, 1% hydroxypropyl methylcellulose) will be prepared in the same single-dose package without preservative, with the same solvent (1% hydroxypropyl methylcellulose). Participants will receive one drop in each eye once per night.

The single-dose containers of eyedrops will be stored in the area only accessible to the investigator who is not masked to treatment. The eyedrops should be stored at room temperature (15-25°C).

Participants and their guardians will be instructed on the administration of eyedrops after recruitment. A 2- or 3-month dosage of eyedrops will be provided at each visit after finishing all the ocular examinations, and all the empty eyedrop containers will be returned at the next visit, to calculate the compliance rate.

The intervention will be discontinued if the guardian or participant requests to withdraw, or participants has severe allergic response, or aggravation of IXT fulfilling the deterioration criteria for two consecutive follow-ups. IXT deterioration criteria will be met by either development of constant exotropia  $\geq 10$  PD at distance and near or presenting with a decrease

in near stereoacuity of at least 2 octaves. When the deterioration criteria are first met, a retest will be performed after a 10-minute break to confirm or refute the result. The participants experiencing deterioration for 2 consecutive follow-ups will be requested to cease the intervention, and then underwent a further two-month observation period. If participants still fulfill the deterioration criteria, surgery will be recommended.

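### With one fixed block size of six, the unmasked investigator who randomises could deduce about 29% of allocations in advance, and the plan does not separate that person from consent, scheduling or the decision to enrol

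*Combined protocol and SAP*

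**What the plan says.** Section 5.1 describes a "2-year, single-center, randomized, double-masked, and placebo-controlled trial". Section 5.7 sets the 2:1 ratio "by use of a block randomization scheme with a fixed block size of six", and no stratification factor is mentioned anywhere. On who operates the scheme, it says: "Randomization will be completed by one unmasked investigator using sealed envelopes that contain randomized numbers". On everyone else: "Other investigators, participants, and the statistician will be masked to study allocation". Section 5.8 adds that the drops are "stored in the area only accessible to the investigator who is not masked to treatment", so the same role also controls the supply.

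The sequence is generated "by a statistician who is not involved in participant recruitment or data collection". Section 5.7 makes no matching statement for the unmasked investigator. It also does not say that the envelopes are opaque or sequentially numbered, or that a child must be irrevocably enrolled before one is opened. Table 1 (Section 5.10) places eligibility assessment, consent, and enrolment with randomisation at the baseline visit, without an order or a division of roles. Section 5.11 assigns the examinations to staff who do not know the treatment.

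**The concern.** Concealment means that whoever can influence a child's entry does not know the next assignment. Here one person sees every assignment as it is made, and the protocol states the block size. Once both placebo slots or all four atropine slots of a block are used, the rest of that block is fixed.

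If that person also has a say in consent, in timing or in the last decision to enrol, children could be steered by expected progression, for example by age. Some criteria in Section 5.5 leave room for judgement: ability to cooperate, the clinical significance of an abnormal finding, and willingness to attend for two years. Intention to treat does not remove an imbalance created before randomisation, and Section 7 names no baseline covariate for the primary comparison. Age and baseline SE appear there only as subgroup factors.

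**Working it through.** **Inputs.** Block size 6, ratio 2:1 and one unmasked randomiser (Section 5.7); one centre (Section 5.1); 300 children as 200:100, difference 0.22 D, SD 0.57 D, 80% power, 5% type I error and 20% drop-out (Section 5.6). Assumption: one unstratified sequence used in order, which the documents imply but do not state.

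**1. The plan's own figure.** Control-arm n = (1 + 1/2) × (1.96 + 0.84)² × 0.57² / 0.22² ≈ 79.0, rounded up to 80, with 160 on atropine. Power at 80 and 160 is 80.5%. Then 240 / 0.8 = 300, which is 300 / 6 = 50 blocks. The sample size reproduces. The plan gives no predictability figure.

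**2. Determined allocations.** A block has C(6,2) = 15 equally likely orders, hence 15 × 6 = 90 positions. A position is determined when every remaining slot is the same arm, so the count per order is the length of its final run.
- Final atropine run of at least k: C(6−k, 2) orders, giving 10 + 6 + 3 + 1 = 20 positions.
- Final placebo run of at least k: C(6−k, 2−k) orders, giving 5 + 1 = 6 positions.
- Total 26 of 90 = 28.9%, or 26/15 = 1.73 per block. Closed-form check: 4/(2+1) + 2/(4+1) = 1.733.
- Over 50 blocks: 50 × 20/15 ≈ 67 atropine and 50 × 6/15 = 20 placebo, together about 87 of 300.

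**3. Benchmark.** Guessing whichever arm has more slots left is right in 67 of 90 positions (74.4%). Always guessing atropine is right 66.7% of the time. The gain is 7.8 points, about 23 of 300 children.

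**4. Alternatives.** Certain allocations under other fixed sizes: 44.4% for blocks of three, 21.4% for nine, 17.0% for twelve. With sizes drawn at random (simulation of 200,000 allocations, observer knows the candidate sizes but not the draws): about 10% for 3/6, 5% for 6/9 and 4% for 3/6/9. Four per cent of 300 is about 12 children.

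**5. Scale of possible bias (illustration only).** The documents give no figure for how far selection could shift progression, so the shift s is assumed. If every determined slot were exploited in favour of atropine, bias = s × (67/200 + 20/100) ≈ s × 0.533.

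| Assumed s | Bias | Share of 0.22 D |
|---|---|---|
| 0.05 D | 0.027 D | 12% |
| 0.10 D | 0.053 D | 24% |
| 0.20 D | 0.107 D | 48% |

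**The case against.** The strongest reply is that only one person could make the deduction, and would have to track the sequence to do so. All other investigators are masked. Most eligibility gates (cycloplegic SE, deviation, acuity, astigmatism, intraocular pressure) are examination results obtained by masked staff under Section 5.11, and only children already found eligible are randomised. About 67 of the 87 determined slots are atropine, which was the likelier arm anyway, and the overall gain in guessing is modest. All of this stands, and it narrows the point to consent, scheduling and the moment of enrolment. It does not close it: masked examinations protect measurement, but do not settle who obtains consent, books the visit or decides to open the envelope.

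A reader might infer three stronger things that the documents do not support.
- That 29% of allocations are simply known beforehand. They are deducible by one role, under the single-sequence assumption.
- That the unmasked investigator does screen or enrol children. The plan neither says nor excludes it.
- That an accidental unmasking, for instance through a visible pupil effect, would let masked colleagues work out neighbouring allocations. The documents give no evidence of such an effect at 0.01%. A colleague would also need the enrolment order and block boundaries. Even then, one known atropine child moves a block-mate's chance of atropine only from 67% to 3/5 = 60%, and one known placebo child to 4/5 = 80%.

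**Conclusion.** The point holds as an avoidable weakness in allocation concealment. The size rests on one unstratified sequence used in order and on an observer who sees all earlier allocations, which describes the unmasked investigator alone. Whether any bias follows depends on that person's influence over entry, which the plan leaves open. Nothing in the documents shows that selection took place, and the bias figures above illustrate scale without estimating it. The change is worth making because it costs little and removes most of the certainty, while the target difference is only 0.22 D.

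**What to change.** For all children not yet randomised:
- Have the statistician generate the list with randomly varying permuted blocks of 3, 6 and 9 at 2:1, with the block sizes withheld from the investigators.
- State in Section 5.7 that the unmasked investigator takes no part in screening, consent or scheduling.
- State that the next sequentially numbered opaque envelope is opened only after a masked investigator has signed eligibility and consent.

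The cost is a new list, new envelopes and a one-paragraph amendment. The role separation calls for a masked investigator to be available to sign at enrolment. The final split may differ from 200:100 by a few children, which matters little for power.

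The documents do not say whether enrolment has begun. If it is already complete, the list cannot be changed. In that case, report who enrolled children, and compare baseline age and SE between determined and undetermined slots, within each arm. With only about 20 determined placebo slots expected, finding no difference would be weak reassurance.
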